#### Exploratory outcomes

Interleukin (IL)-6, IL-8, and small-molecule metabolites will be monitored to explore the mechanism of PSD at baseline and weeks 4 and 8. Serum inflammatory cytokines such as IL-6 [31] and IL-8 [32], which are shown to participate in the pathological processes of both stroke and depression and provide some prediction values, will be detected using enzyme-linked immunosorbent assay (ELISA) techniques.

#### Safety measures

Safety measures will include vital signs, results of electrocardiography, a complete blood count, kidney and liver function tests (include blood lipid panel: total cholesterol, triglycerides, high-and low-density lipoproteins). All adverse events will be followed from the time of randomization to up to 16 weeks after the end of intervention.

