## Background

Post-stroke depression (PSD) is one of the most common complications of stroke and is characterized by depressed mood, generalized anxiety, and apathy [1–3]. The prevalence of PSD is approximately one third of stroke survivors at any one time [4], ranging from 39% to 52% within the first 5 years [5]. PSD patients experience poor functional outcomes [6] and increased mortality [7]. Several therapeutic strategies have been shown to be effective for PSD, including pharmacological, non-pharmacological interventions (e.g., psychotherapy, electroconvulsive therapy, and acupuncture), and combination therapies [8]. The most frequently studied agents are antidepressants, whereby the most thoroughly characterized agents are selective serotonin reuptake inhibitors (SSRIs) (e.g., fluoxetine, sertraline, citalopram) and serotonin and norepinephrine reuptake inhibitors (SNRIs) [9]. However, antidepressant medications exhibit a series of side effects, such as increased risk of hemorrhagic complications and stroke [10], although minor side effects such as nausea, diarrhea, fatigue, and dizziness are most commonly reported.

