Traditional Chinese medicine (TCM) has been used to treat PSD and has demonstrated a more favorable safety profile than conventional medicine. A meta-analysis showed that *Liver-qi* regulation effectively ameliorates depressive symptoms, as well as enhancing quality of life among patients with PSD [11]. According to a data from a previous  research about the syndrome differentiation of ischemic stroke, the syndrome of *“qi deficiency* and *blood stasis”* might reach a proportion of 21.54% among the clinical patients, which would rank first within the different subtypes [12]. As a common complication of stroke, PSD can be divided into different syndromes, among which qi deficiency and blood stasis is an important subtype [13, 14]. *Jiedu Tongluo* granules (JDTLG) is a patented complex Chinese medicine formulation (No: 201510419571.3), which consist of seven herbs, including *Panax ginseng* (*Ren Shen*) 12.5 g/100 g, *Ginkgo biloba* (*Yin Xing Ye*) 25 g/100 g, *Hypericum perforatum L.* (*Guan Ye Lian Qiao*) 12.5 g/100 g, *Scutellaria baicalensis Georgi* (*Huang Qin*) 12.5 g/100 g, *Gardenia jasminoides Ellis* (*Zhi Zi*) 12.5 g/100 g, *Gastrodia elata Bl.* (*Tian Ma*) 12.5 g/100 g, and *Ligusticum chuanxiong hort* (*Chuan Xiong*) 12.5 g/100 g. According to the TCM theory, these herbs are believed to supplement *qi* and activate blood circulation, remove toxins and relieve stagnation, extinguish *wind*, and dredge collaterals. One previous study showed that JDTLG significantly improved depression-like behavior in animal stroke models [15]. *Panax ginseng* and *Ginkgo biloba*, key components of JDTLG, are known to possess neuro-protective effects [16–20]. Furthermore*, the antidepressant effects of Panax ginseng* [21] and *Ginkgo biloba*’s [22] might be derived from activation of the signaling pathway involving brain derived neurotrophic factor (BDNF). Our preclinical pharmacological experiments have shown that JDTLG has a neuroprotective and anti-apoptotic effect via up-regulating the expression of BDNF, hypoxia-inducible factor 1-alpha (HIF1α), cAMP-response element binding protein (CREB) and reducing the expression of vascular cell adhesion molecule1 (VCAM1) and matrix metallopeptidase 9 (MMP9). In addition, JDTLG can exert an anti-depressant function through increasing the expression of tropomyosin receptor kinase B (TrkB), mammalian target of rapamycin (mTOR), and 5-hydroxytryptamine (5-HT) receptor (unpublished data).

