### Intervention

Participants will be allocated to receive JDTLG or placebo for 8 weeks in addition to their usual conventional treatment (e.g., antiplatelet, lipid-lowering, antihypertensive, or antidiabetic therapy). The JDTLG and placebo granules (3.9 g/sachet) will be taken orally with warm water twice a day for 8 weeks. Product will be provided by China Resources Sanjiu Medical and Pharmaceutical Co., Ltd., Shenzhen, China (Production batch number: 161001 W). Analyses have shown that the quality of JDTLG is consistent with the Chinese Medicine Standards of the State Food and Drug Administration (SFDA). Active granules contain 3.9 g of JDTLG each, which is equivalent to 24 g of crude medicine. Placebo granules are composed of 10% crude JDTLG and 90% starch and are of identical appearance and smell as the active granules. Participants will be instructed to refrain from all other Chinese herbal decoctions or medicines used to treat PSD during the study. Participants can withdraw from the study and choose modern medical treatments, such as SSRI antidepressants, when their depressive symptoms worsen. All of the unused granules will be asked to be returned to the trial team and reasons of not taking the medicine will be recorded on the CRF.

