### Safety assessment

Safety evaluation will be based on the incidence of adverse events (AEs) including clinically significant changes identified during physical examinations, vital signs (temperature, blood pressure, breathing and heart rate), and standard clinical laboratory tests (complete blood count, liver and renal function tests). Participants will be asked to report any abnormal events occurring at any time during the trial to the investigators. All details of related and unexpected AEs will be recorded on Case Report Forms (CRF). Safety will be monitored every 4 weeks, and for up to 16 weeks after the end of intervention.

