## Discussion

Depression is common after stroke and is related to with poor functional outcome and high mortality [33]. The association between depression and stroke has been established whereby stroke has been shown to increase the risk of PSD, and conversely, depression has been shown to be an independent risk factor for stroke [34]. The most commonly used antidepressants are SSRI and SNRIs, although they are not without side effects including increasing risk of hemorrhagic complications. As antidepressant medications have the potential to cause a series of adverse effects and are associated with poor patient compliance, it is important to explore other effective treatments that may have fewer side effects in the management of PSD. Chinese herbal medicine has the potential to offer an effective and safe treatment for PSD.

In this trial, we will investigate whether the JDTLG plus conventional treatment can reduce depression and improve daily living ability among participants who have recently suffered a stroke. We have previously shown that JDTLG effectively treats PSD in a rat model. This study will be conducted as a randomized, double-blind, placebo-controlled pilot crossover trial to provide evidence for the clinical efficacy of JDTLG.

The purpose of this prospective trial is to prove the therapeutic efficacy and safety of JDTLG. The outcome of the trial will provide evidence-based data regarding whether JDTLG is beneficial for PSD participants with qi deficiency and blood stasis syndrome. More importantly, the success of this study will support a large-scale clinical study to further consolidate the evidence for the use of JDTLG in PSD patients with qi deficiency and blood stasis syndrome.

This study has several limitations that require consideration. Firstly, as the study is being undertaken in one center; therefore, it may not necessarily be possible to extrapolate these results to other regions or ethnic groups. Secondly, the sample size is small and the treatment period short. However, this data will inform a subsequent multi-centered study compromising a sufficient sample size over a longer treatment period.

In conclusion, this prospective study will demonstrate that the JDTLG with conventional treatment is able to effectively and safely treat PSD with qi deficiency and blood stasis syndrome, thereby providing a new direction for treating PSD with minimal side effects.

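### Bleeding and recurrent stroke are held against antidepressants but named in no safety measure, and the CRF rule for adverse events conflicts with the promise to follow and analyse all of them

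*Protocol article*

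**What the plan says.** **Motivation.** The Background gives antidepressants side effects "such as increased risk of hemorrhagic complications and stroke"; the same sentence adds that nausea, diarrhoea, fatigue and dizziness are the ones most often reported. The Discussion says of SSRIs and SNRIs, "although they are not without side effects including increasing risk of hemorrhagic complications", mentions poor compliance as well, and closes by stating that the trial will show JDTLG to be effective and safe, with side effects it calls minimal.

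**Population and setting.** The Inclusion criteria ask for a clinical diagnosis of stroke without limiting its type. The only stroke-related exclusion is stroke secondary to tumour or trauma. Under Intervention, the granules are given "in addition to their usual conventional treatment (e.g., antiplatelet, lipid-lowering, antihypertensive, or antidiabetic therapy").

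**Safety measures.** The section of that name says: "Safety measures will include vital signs, results of electrocardiography, a complete blood count, kidney and liver function tests", the last including a lipid panel. The Abstract and Safety assessment give similar lists. None names bleeding or recurrent stroke.

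**Adverse events.** Safety measures says that all adverse events are followed from randomization. Withdrawal and discontinuation says that all adverse effects are analysed whether or not they are thought related. Safety assessment asks participants to report anything abnormal, but on recording it says: "All details of related and unexpected AEs will be recorded on Case Report Forms". Withdrawal and discontinuation also treats as invalid the data of participants with unrelated complications, one example being a substantial change in the state of their disease.

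**The concern.** A safety conclusion is a stated aim of the trial, and bleeding is the one specific antidepressant side effect that the Discussion names. A reader will therefore look to the trial for evidence on bleeding and on further strokes. Whether that evidence exists depends on general adverse-event reporting, because no safety measure names either event. Both events are easy to classify out of the record under the wording of Safety assessment: a bleed in someone on an antiplatelet can be called expected or unrelated, and so can a second stroke in a stroke patient. If they are left off the CRF, the promise to analyse all adverse effects has nothing to work on, and a clean table could reflect the recording rule rather than the product.

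**Working it through.** The article gives no event rate and no power calculation, so there is no figure of its own to reproduce. The check is mainly a comparison of text, followed by arithmetic on what 40 participants per arm (Sample size calculation) can show.

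**1. The adverse-event rules side by side.**
- Following: all events (Safety measures).
- Analysis: all, regardless of relatedness (Withdrawal and discontinuation).
- Recording on the CRF: details of related and unexpected events (Safety assessment).
- Validity: data of participants with certain unrelated complications are invalid (Withdrawal and discontinuation).

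The recording rule can be read in two ways. If an event must be both related and unexpected, it is lost when it fails either test. If either property is enough, it is lost when judged unrelated and expected. Under both readings some events that are to be analysed have no stated route to the CRF, and no other sentence in the article supplies one. The invalidity rule could cover a recurrent stroke, and it stands in the same section as the promise to analyse everything.

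**2. Do other measurements substitute?** Only indirectly. Blood count and physical examination may show a substantial bleed. NIHSS, mRS and BI are collected every 4 weeks, but Statistical analysis treats them as counts of improved cases, so a new stroke would appear there only as a participant who did not improve.

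**3. What zero events would mean with complete recording.** The exact upper limit for 0 of n is 1 − α^(1/n), with n = 40.
- One-sided 95%: 1 − 0.05^(1/40) = 7.2%.
- Two-sided 95%: 1 − 0.025^(1/40) = 8.8%.

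The chance of at least one event in 40 is 1 − (1 − p)^40. For assumed true risks of 0.5%, 1%, 2% and 5% this is 18%, 33%, 55% and 87%.

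**4. What a comparison of arms could show.** With no events on placebo, Fisher's exact test gives p = 0.055 for 5 events on JDTLG and p = 0.026 for 6, so 6 are needed. For assumed risks of 2% against 10%, power at 40 per arm is 32% by normal approximation and 11% by Fisher's test.

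**5. Under-recording, as illustration only.** If the true incidence over follow-up is p and a fraction c of events is recorded, the chance that 40 participants yield none is (1 − pc)^40. Both p and c are assumptions; the article gives neither.
- p = 10%: 0.90^40 = 1.5% at c = 1; 0.95^40 = 13% at c = 0.5; 0.975^40 = 36% at c = 0.25.
- p = 5%: 0.95^40 = 13% at c = 1; 0.975^40 = 36% at c = 0.5; 0.9875^40 = 60% at c = 0.25.

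**The case against.** The strongest reply is that a bleed or a second stroke is an adverse event. All adverse events are followed, all are analysed whatever their relatedness, participants are asked about anything abnormal, and significant changes on examination or in laboratory tests count as events. A condensed article may also leave a list of events of special interest, CRF questions and tables to the full protocol. Most of this stands, and it rules out several stronger readings:

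- A reader might infer that these harms cannot be judged at all, or reach the data only when volunteered. The all-event wording and the examinations contradict that.
- A reader might infer that bleeding and stroke are the whole case against antidepressants. The article also cites commoner minor effects and poor compliance.
- A reader might infer a pharmacological bleeding hazard from the phrase "activate blood circulation, remove toxins and relieve stagnation". The Background offers it as a belief of TCM theory, and the article reports no bleeding risk for JDTLG.
- A reader might take the absence of a display by stroke type as a defect. Such a table may sit in the analysis plan.

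The reply does not dispose of the recording rule. That rule is printed, it conflicts with two other sections, and no fuller document is needed to see the conflict. It affects every adverse event, but it matters most for events that are easily called expected or unrelated. It is also fair to say that better recording supplies neither power nor an antidepressant comparator.

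**Conclusion.** The point holds in this form: the article's rules for recording and validity contradict its promise to follow and analyse all adverse events, and the two harms that it cites against antidepressants are named in no safety measure. If the narrower rules are followed, bleeding and recurrent stroke cannot be reliably judged.

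How many events would be lost is unknown. The under-recording probabilities rest on assumed incidence and capture, and show only that a falsely clean result is possible. The firm figure is the limit on the conclusion: even with full recording, 0 of 40 is compatible with a true risk of up to 8.8% (two-sided 95%). In a pilot that the article itself describes as not fully powered, and that has no antidepressant arm, a claim of minimal side effects on these harms would go beyond the data. The change should be made. It does not put the primary efficacy analysis in question.

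**What to change.** - Reconcile Safety assessment with Safety measures and Withdrawal and discontinuation, so that every adverse event is recorded on the CRF whatever its relatedness or expectedness, with both judgements entered as separate fields.
- State that the invalidity rule in Withdrawal and discontinuation does not remove safety data.
- Name bleeding events and recurrent stroke as safety outcomes, and ask about them with one fixed CRF question at each existing 4-weekly visit.
- Tabulate both by arm with exact confidence intervals.
- Word the safety conclusion in line with those intervals instead of calling side effects minimal.
- Optionally, describe these events by stroke type. With 40 per arm this is description only.

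The cost is one question per existing visit, one table and a few sentences. No visit, laboratory test or treatment rule is added. The downside is that more minor events will be listed, so the profile may look somewhat less favourable. Because recruitment had already started, events seen but not entered would have to be recovered from source records where possible.

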### Safety assessment

Safety evaluation will be based on the incidence of adverse events (AEs) including clinically significant changes identified during physical examinations, vital signs (temperature, blood pressure, breathing and heart rate), and standard clinical laboratory tests (complete blood count, liver and renal function tests). Participants will be asked to report any abnormal events occurring at any time during the trial to the investigators. All details of related and unexpected AEs will be recorded on Case Report Forms (CRF). Safety will be monitored every 4 weeks, and for up to 16 weeks after the end of intervention.

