## Methods/design

### Study design

This is a double-blind, randomized, placebo-controlled, pilot trial designed to evaluate the safety and efficacy of JDTLG in treating PSD with qi deficiency and blood stasis syndrome. Eighty participants with PSD will be recruited from Xiyuan Hospital of China Academy of Chinese Medical Sciences. After obtaining written informed consent from participants or their legal guardian, participants will be randomly assigned to either the treatment or placebo group with a ratio of 1:1. Participants will undergo an 8-week treatment period and an 8-week follow up. The protocol design is based on the Consolidated Standards of Reporting Trials (CONSORT) guidelines and Standard Protocol Items: Recommendations for Interventional Trials (SPIRIT) Checklist (see Additional file 1).

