### Withdrawal and discontinuation

Participants are able to voluntarily withdraw at any time during the trial. Participants who fail to complete the study, regardless of time or reason, will be considered as dropouts. The last recorded data for these participants will be included in data analyses. Data obtained from participants who experience unrelated complications, such as substantial change in disease status, exacerbation of depression or commence medication that could potentially interfere with JDTLG, will be treated as invalid. Withdrawal due to adverse events will be distinguished from withdrawal due to insufficient response. All adverse effects will be analyzed at the endpoint of the trial regardless of whether they are deemed related to the trial medication or not. If a participant withdraws due to a serious adverse event, it will be reported in accordance with the reporting requirements. Where appropriate, data collected by these participants will be used in intention-to-treat analyses.

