### Study visits and procedures

The visit schedule for all evaluations (baseline, primary outcomes, secondary outcomes, exploring outcomes and safety indicators) is shown in Table 1. Participants will be assessed by the same investigator at each assessment. Baseline measurements, demographic characteristics, and medical history will be collected at the first visit only. All concomitant medications will be recorded during the treatment period (i.e., baseline to 8 weeks), including the name, dosage, and course of these medications. Primary and secondary outcomes and safety indicators will be collected every 4 weeks from baseline until week 16.

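### The adverse-event rules contradict each other on which events are recorded and on when safety follow-up ends (week 16 or week 24)

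*Protocol article*

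**What the plan says.** **Which events.** The article gives one rule for entering adverse events on the case report form, under Safety assessment: "All details of related and unexpected AEs will be recorded on Case Report Forms (CRF"). Other statements are wider:

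- Withdrawal and discontinuation: "All adverse effects will be analyzed at the endpoint of the trial regardless of whether they are deemed related" to the trial medication or not.
- Safety measures says that all adverse events are followed.
- Safety assessment itself bases the evaluation on the incidence of adverse events, with no limit by cause, and asks participants to tell the investigators of any abnormal event.

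**How long.** Two sections give a longer window:

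- Safety measures: "All adverse events will be followed from the time of randomization to up to 16 weeks after the end of intervention".
- Safety assessment: "Safety will be monitored every 4 weeks, and for up to 16 weeks after the end of intervention".

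Two sections give a shorter one:

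- Study design: "Participants will undergo an 8-week treatment period and an 8-week follow up".
- Study visits and procedures: "Primary and secondary outcomes and safety indicators will be collected every 4 weeks from baseline until week 16".

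**The concern.** Safety is in the title, the aim and the conclusion of the article, so the adverse-event count is a main result of this pilot. That count depends on which events are written down and over what period. The text gives two answers to each question.

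A recording rule that depends on relatedness and expectedness filters events at entry, according to the investigator's opinion. In stroke patients on antiplatelet, lipid-lowering, antihypertensive or antidiabetic treatment, many events could plausibly be put down to the illness or to other drugs. An event that never reaches the case report form cannot be recovered by any later analysis plan, so this is not a detail that an unseen plan could settle.

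The two end dates mean that investigators may stop collecting at different times, and that a reported incidence could refer to 16 or to 24 weeks.

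**Working it through.** **Step 1: does the recording rule cover all events?** Classify events by relatedness and expectedness. The phrase in the rule can mean that an event is entered if it has either attribute, or only if it has both.

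| Event | Entered if either attribute suffices | Entered if both are needed | Needed for the analysis promised under Withdrawal and discontinuation |
|---|---|---|---|
| Related, unexpected | yes | yes | yes |
| Related, expected | yes | no | yes |
| Unrelated, unexpected | yes | no | yes |
| Unrelated, expected | no | no | yes |

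The wider reading leaves out one class of the four and the narrower reading leaves out three. Neither gives all events. The documents give no event rates by class, so the share of events affected cannot be computed from them.

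**Step 2: when does safety follow-up end?** Inputs: 8 weeks of treatment and 8 weeks of follow-up (Study design); 16 weeks after the end of intervention (Safety measures, Safety assessment); 4-weekly collection until week 16 (Study visits and procedures); 40 participants per group (Sample size calculation).

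- Study design: 8 + 8 = week 16. This reproduces the end date in Study visits and procedures, with visits at weeks 0, 4, 8, 12 and 16.
- Safety measures and Safety assessment: 8 + 16 = week 24. At the same 4-weekly spacing this adds contacts at weeks 20 and 24.
- Difference: 24 − 16 = 8 weeks. This is 8/24 = one third of the longer window, and 8/16 = half of its post-treatment part.
- Observation time at stake, with 40 per arm and no dropout: 40 × 8 = 320 person-weeks per arm, or 640 in total. Per arm this is 40 × 24 = 960 person-weeks against 40 × 16 = 640.

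**Step 3: can the dates be read as agreeing?** If the 16 weeks were counted from randomisation, the window would end at week 16 and the conflict would disappear. But both safety sections count from the end of the intervention, so the text does not support that reading.

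**The case against.** The strongest reply is that the recording sentence does not say that other events go unrecorded. It may only demand full detail for one class. The surrounding text favours broad capture: participants report anything abnormal, all events are followed, incidence is unrestricted, the trial follows ICH Good Clinical Practice, and vital signs, electrocardiography and laboratory tests are collected without a causality filter. This has weight. It shows that the text is contradictory, not that events are certain to be lost. It does not remove the point, because no other sentence says how the remaining events are to be recorded, and Data management and quality control makes the case report form and the data system the route to analysis.

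On timing, the longer window is worded as a maximum, and following an event may differ from collecting safety indicators at a visit. That softens the conflict, but Study design still allows only 8 weeks after treatment.

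Three stronger readings are tempting, and the documents support none of them:

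- *The promised analysis is impossible.* That would be so only if the narrower rules were the ones followed. No single statement promises an analysis of all events over 24 weeks: the analysis promise refers to the end of the trial, and the longer window comes from other sections.
- *Nobody is seen between weeks 16 and 24.* Study visits and procedures lists no such visit, but Safety assessment can be read as 4-weekly monitoring to week 24, and the content of Table 1 was not available for this check.
- *The filter favours the active arm.* Participants and attending physicians are blinded until study completion, so relatedness would be judged blind, and the same rules apply to both arms. The likely harm is undercounting, not a shown bias between arms.

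The trial is also an exploratory pilot that is not fully powered, and its primary outcome at week 8 is untouched.

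**Conclusion.** The point holds as two internal contradictions in the current text.

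1. The only recording rule is narrower than the promised analysis, the stated follow-up of all events and the section's own basis in overall incidence. If followed literally, adverse-event incidence would be undercounted in both arms, by an amount that the documents do not allow to be estimated.
2. Safety follow-up ends at week 24 in two sections and at week 16 in two others, a difference of 8 weeks. The 320 person-weeks per arm is an upper figure that assumes 40 per arm and no dropout.

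The documents do not show which end date is intended. This should be fixed, since it touches a headline objective and costs little. It does not threaten the primary efficacy analysis.

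**What to change.** - **Recording.** Reword the sentence under Safety assessment to agree with Withdrawal and discontinuation: every reported adverse event is entered on the case report form, with relatedness and expectedness recorded as attributes of the event and not as conditions for entry. Compare the arms on all events.
- **Window.** Reconcile Study design, Safety measures, Safety assessment, and Study visits and procedures to one stated end of safety follow-up, the same in both arms, and make the visit schedule match it. The choice of date belongs to the sponsor and the investigators.

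**Cost.** Protocol wording and slightly more data entry at existing visits. If the longer window is the intended one, contacts after week 16 must also be added to the schedule; at the 4-weekly spacing these are weeks 20 and 24. The article reports that recruitment is under way, so an early correction would limit the number of participants followed under the conflicting text.
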